**Methods/design:**

The aim is to recruit 64 cancer survivors 2-6 months after completion of chemotherapy, usually adjuvant, with curative intent. Subjects will be recruited through oncology clinics in a single institution and randomised to usual care or an exercise intervention. The exercise intervention consists of two specifically tailored supervised moderate intensity aerobic exercise sessions weekly over 8-weeks. All participants will be assessed at baseline (0 weeks), at the end of the intervention (8 weeks), and at 3-month follow-up. The primary outcome measure is fitness, and secondary patient-related outcome measures include fatigue, quality of life, and morphological outcomes. A further secondary outcome is process evaluation including adherence to and compliance with the exercise program.

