### Patient Recruitment

Participants will be sourced from the institutional cancer database, by invitation from study personnel in cancer clinics and directly from the oncology service in St. James's Hospital, Dublin, Ireland. Study personnel will provide further information to these patients and assess them for eligibility. Ethical approval has been approved from the institutional Research Ethics Committee and informed consent will be gained from each participant prior to study inclusion.

Aerobic fitness will be measured using the Modified Bruce treadmill test and those with aerobic fitness levels average or below age- and gender norms [37] and meeting other inclusion criteria will be invited to participate in the study. Subjects scoring average or below for age and gender cut-off levels according to the Modified Bruce Protocol, will be randomized to the exercise intervention or usual care.

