### Assessment

Post randomization follow-up will be at baseline (week 0), end programme (8 weeks) and 3 month follow-up.

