#### Outcome Measures

##### Primary Outcome measure: Fitness

Physical fitness will be measured by the Modified Bruce Protocol. A sub-maximal test was chosen over a maximal test for this population because of safety and motivational concerns [39]. Verbal encouragement during the exercise test will be standardised.

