### Statistical analysis

Randomization will be by a computer-generated random numbers list (GraphPad Software, San Diego, CA) with intention-to-treat as the primary analysis and per protocol as the secondary analysis.

Assuming a difference of 5 mL/kg/min^-1^, with a SD of 6.5, and a 5% significance (two-sided) and 80% power, 28 participants would be required per group. However, the goal would be to accrue 32 subjects to allow for a 15% drop out rate and subgroup analyses. One year will be allowed for accrual of participants. The drop-out rate is calculated to include patients who are unfortunately diagnosed within 3 months of the final assessment as having a relapse of their cancer. As occult return of cancer could have a negative impact on fitness and capacity to exercise, these patients' data will be excluded from the primary outcome measure but included in the process analysis. The same will be done for the data of any participant on anti-Her2 therapy in whom an LVEF assessment during the study or within 3 months of the end of the study has a drop in LVEF to < 50% or by > 20% compared to baseline, as, similarly, occult ongoing myocardial toxicity could have a negative impact on fitness.

We will provide descriptive data and 95% CIs for all possible comparisons. For our primary analysis, we will use the intent-to-treat principle and for the secondary analysis, per-protocol analysis. In sensitivity analyses (intent-to-treat), the impact of missing values will be studied by using a range of imputed change scores for missing values, and by analysing those subjects who provide complete data. Repeated measured of analysis (ANOVA) will be used across more than two time points for continuous data. Mixed-model analysis will be used to model each outcome measure at three (or two) time points and compare the differences across groups over time for non-continuous data. We will use t-tests between 2 groups when data are normally distributed and the Mann-Whitney U test will be used when data are non-normally distributed. The Chi-squared test will be used for categorical data. Tests for interaction will be carried out for the effect of gender and type of cancer.

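### The plan powers one two-group difference in fitness but does not say which visit or which test is primary, and no listed method uses the pre-randomisation fitness value as a covariate

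*Protocol article*

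**What the plan says.** The primary outcome is named without a time point: "Physical fitness will be measured by the Modified Bruce Protocol" (Primary Outcome measure: Fitness). The abstract gives three assessments: "All participants will be assessed at baseline (0 weeks), at the end of the intervention (8 weeks), and at 3-month follow-up". Two of these come after baseline, and neither is called primary.

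The Statistical analysis section sizes the trial on one two-group comparison: "Assuming a difference of 5 mL/kg/min^-1", "with a SD of 6.5", two-sided 5%, 80% power, 28 per group. It does not say at which visit the difference applies, or whether the SD is of final values or of change.

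For analysis, the same section lists repeated-measures ANOVA for continuous data at more than two time points. It then adds: "We will use t-tests between 2 groups when data are normally distributed and the Mann-Whitney U test will be used" for data that are not normal. It promises confidence intervals for every comparison. For the primary analysis, intention-to-treat is the only feature it fixes.

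On baseline, Patient Recruitment states: "Aerobic fitness will be measured using the Modified Bruce treadmill test". That result decides eligibility, so it exists before randomisation. The Assessment section, however, says: "Post randomization follow-up will be at baseline (week 0), end programme (8 weeks) and 3 month follow-up".

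**The concern.** Fitness is continuous and measured at three visits, so it meets the stated condition for the ANOVA. It also meets the condition for a two-group test at either follow-up visit. These procedures answer different questions. A t-test at week 8 estimates the difference that was powered. A Mann-Whitney test compares distributions. A group-by-time test over three visits spends two degrees of freedom and gives no single difference in mL/kg/min. A reader of the results could not tell which one was meant to decide the trial.

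Two things are at stake. The first is error control: with the visit and the analysis left open, the 5% level protects the conclusion only if one choice was fixed beforehand. The second is precision. Baseline fitness is likely to predict later fitness, and every participant already has the value. A two-group test on follow-up values makes no use of it, and the trial is small.

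**Working it through.** **Inputs from the document.** Difference 5 mL/kg/min, SD 6.5, two-sided 5%, 80% power, 28 per group (Statistical analysis). Two follow-up visits (abstract).

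**Assumptions.** The correlation r between visits is not given, so a range of 0.3 to 0.8 is used. The SD is read both ways, as of final values and as of change.

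**1. The plan's own figure.** The standardised difference is 5/6.5 = 0.769. An exact two-sample t-test needs 27.5 per group, rounded up to 28, which matches. With 28 per arm, SE = 6.5 × √(2/28) = 1.74, and power by the noncentral t is 80.7%. The powered comparison is therefore a two-group t-test at one visit.

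**2. The normality rule alone.** In simulation with 28 per arm under no effect, choosing between t and Mann-Whitney by a normality test at one visit gave 4.9 to 5.4% false positives with normal data and 4.5 to 5.1% with skewed data. Reporting whichever of the two was significant gave about 6%, but the plan does not provide for that.

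**3. The open choice of visit.** If a significant result at either visit were accepted, the error is 1 − P(|Z₁| < 1.96 and |Z₂| < 1.96), with correlation r between the two statistics:

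| r | Error |
|---|---|
| 0.3 | 9.5% |
| 0.5 | 9.1% |
| 0.7 | 8.3% |
| 0.8 | 7.8% |

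If the ANOVA group-by-time test were a further route to success, simulation with normal data gives 12.3 to 12.8% for r 0.5 to 0.8.

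**4. Baseline adjustment (ANCOVA), 28 per arm, difference 5.** If 6.5 is the SD of final values, the residual SD is 6.5 × √(1 − r²). If 6.5 is the SD of change, it is 6.5 × √((1 + r)/2). In each case SE = residual SD × √(2/28).

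| r | SE, final values | Power | SE, change | Power |
|---|---|---|---|---|
| 0.3 | 1.66 | 84.2% | 1.40 | 93.9% |
| 0.5 | 1.50 | 90.4% | 1.50 | 90.4% |
| 0.7 | 1.24 | 97.7% | 1.60 | 86.5% |
| 0.8 | 1.04 | 99.7% | 1.65 | 84.6% |

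The comparator in both columns is the unadjusted test on the matching scale, with SE 1.74 and power 80.7%.

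**5. The ANOVA's group-by-time test.** It includes baseline as a visit and so uses it. Simulated power (SD of final values, difference 5 at week 8, several patterns at 3 months) was 56 to 70% at r = 0.3, 72 to 84% at 0.5 and 91 to 98% at 0.7. ANCOVA at week 8 gave 83 to 84%, 89 to 90% and 97 to 98%. At r = 0.8 the two are nearly equal (98.6 to 99.8% against 99.7%). At the lower correlations this route can fall below the planned 80%.

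**The case against.** The case for the plan is substantial in several respects.

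- **The planned test meets its target.** The t-test has the stated 80%, so a reader who infers that the trial is underpowered goes too far. Adjustment is an available gain.
- **The normality rule is not an error-inflating device.** One might infer that three listed tests mean three chances at significance. Under the stated rule, however, t and Mann-Whitney exclude each other, and the rule by itself holds the error near 5%. Its remaining fault is that the data decide the primary test and what it estimates.
- **Baseline is not wholly ignored.** The ANOVA's group-by-time term uses it. The narrower statement stands: no listed method uses it as a covariate.
- **The plan states no either-visit rule.** The 8 to 9.5% is therefore conditional. Because the intervention lasts 8 weeks and the later visit is called follow-up, week 8 is the natural reading, but it is nowhere stated.
- **A diluted ANOVA main effect cannot be charged to the plan.** A true difference of 5 at both follow-ups averages to (0 + 5 + 5)/3 = 3.3 over three visits, but the plan never names that main effect as its test.
- **A condensed article may leave covariates and details to a fuller document.** That covers silence. It does not cover competing tests that the article does list for one outcome, which do not all match the comparison that was powered.

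**Conclusion.** The point holds in limited form. The document fixes neither a primary visit nor a primary test for fitness, and its listed analyses compete for that role. It does not show a trial that lacks its planned power or one that must exceed 5% error.

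The error exposure is about 8 to 9.5%, and only if success at either visit were accepted, with between-visit correlation assumed at 0.8 to 0.3. The forgone gain from baseline adjustment is from 80.7% power to about 84 to 99.7% if 6.5 is the SD of final values, or to about 85 to 94% if it is the SD of change, with r assumed at 0.3 to 0.8. The upper figure of 99.7% belongs only to the first reading at r = 0.8 and should not be quoted alone. Entry is limited to people of average or lower fitness, which may reduce r.

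The wording conflict over baseline is minor. Patient Recruitment places the treadmill test before randomisation, while Assessment lists baseline under post-randomisation follow-up. This does not show that baseline fitness was compromised.

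**What to change.** State one primary test in the Statistical analysis section: the between-arm difference in fitness in mL/kg/min at week 8, adjusted for the pre-randomisation treadmill value, by ANCOVA or the week-8 contrast of a mixed model, at two-sided 5%. Make the 3-month comparison secondary. Drop the normality-driven choice for the primary outcome and keep the rank test as a sensitivity analysis. Say whether the SD of 6.5 is of final values or of change. Reword the Assessment section to agree with Patient Recruitment, so that baseline is described as measured before randomisation.

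The cost is wording only. The baseline value is already collected for eligibility, and the sample size need not change.

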## Discussion

This study will assess the effect of a novel 8-week exercise programme in cancer survivors 2-6 months post cessation of adjuvant therapy. No intervention studies to date have explored a relatively short individually prescribed exercise intervention in a heterogeneous cancer population in terms of physiological and process outcomes. This study will provide valuable insights into the effect and feasibility of this type of programme and if successful would be clinically transferable to a broad range of cancer settings.
